## Abstract

**Background:**

Patients with borderline personality disorder (BPD) experience significant affect regulation difficulties that cause serious consequences in their work, emotional, and social environments. This dysfunctional pattern also produces great suffering and a heavy burden on their relatives. Fortunately, some studies show that treatment of relatives of people with BPD begins to be important in the patients’ recovery and in improving family dynamics. One of the treatments that has obtained the most empirical support is Family connections (FC). This 12-session program is an adaptation of different Dialectical Behavior Therapy strategies. To test the efficacy of FC, five uncontrolled clinical trials were conducted, with pre-post treatment and follow-up assessments. The results of these studies and subsequent replications showed an improvement in family attitudes and caregiver burnout. Our research team adapted FC for delivery in the Spanish population. We intend to test the efficacy of this program versus a treatment as usual condition. Moreover, we aim to test the efficacy of this program and study its effectiveness (in terms of participants’ acceptance). This paper presents the study protocol.

**Methods:**

The study is a randomized controlled trial. The participants will be recruited in a Personality Disorders Unit and randomly assigned to one of two treatment conditions: *Family Connections group (FC)* or Treatment As Usual (TAU). Primary outcome measures will be the BAS and FAD-GFS. Secondary outcomes will include DASS-21, FES, GS, and QLI. Participants’ treatment acceptance and degree of satisfaction will also be measured. Participants will be assessed at pre-, post-treatment, and 6-month follow-up. Intention to treat and per protocol analyses will be performed.

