This study has several objectives. First, we aim to test the efficacy of FC for relatives of patients with BDP in an RCT with a sample of participants from specialized care in Spain, compared to Treatment as Usual (TAU), that is, an active treatment condition. Second, we will study the feasibility and acceptance of this intervention protocol in family members of patients with BPD. Third, we intend to study whether changes in family members’ disease burden and clinical symptoms are related to the improvements observed in patients with BPD. Fourth, we aim to study whether the changes that may occur in relatives with regard to disease burden and clinical symptoms are related to the family climate. Finally, we will study the perceptions and opinions of families and patients about both intervention protocols.

We hypothesize that: a) both interventions will result in significant reductions in distress and burden and improvements in overall family functioning at post-treatment, and these results will be maintained at the 6-month follow-up; b) the FC program will significantly outperform the TAU intervention on measures of subjective burden, validation skills, family functioning, and quality of life; c) both protocols will be well accepted, but FC will be rated significantly higher by the participants; d) the improvement that may occur in the family members with regard to disease burden and clinical symptoms will have a positive influence on the family climate; e) in an exploratory way, given the lack of specific data in the literature, we hypothesize that the changes observed in the relatives will be related to the clinical evolution of the patients. In this article, we present the study protocol.

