### Sample size

To determine the sample size, the effect sizes found in the literature on the subject have been considered. The controlled study by Grenyer et al. [35], which tested a group psychoeducation protocol for caregivers of people with BPD, reported medium to large effect sizes (dyadic adjustment, *d* = .78; family empowerment, *d* = 1.4). In addition, on measures of burden, Grenyer [35] reported significant improvements between post assessment and the 12-month follow-up, with medium effect sizes (Burden Assessment Scale, *d* = .45). These effects are consistent with the literature on psychological treatments for other psychiatric disorders, such as the meta-analysis of psychological interventions for caregivers of people with bipolar disorders (Burden, *g* = −.80) [36].

Taking these data into account, in the present study, adopting a conservative approach, an effect size of 0.60 is expected because our design includes two experimental conditions. Considering an alpha of 0.05 and a statistical power of 0.80 on a 2-tailed *t* test, the total sample size needed to reach an effect size of 0.60 for burden is 90 participants (45 participants per experimental condition). To control the maximum possible loss of participants during treatment, based on the literature about programs for family members of patients with BPD, a 29% dropout rate is expected [20, 23–25, 27]. Thus, the required sample size should be a total of 116 participants (58 participants per group). These calculations were made with the software program G*Power 3.1 [37].

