### Data analyses

In order to analyze whether there are differences between the experimental conditions before the application of the treatment, Student’s t tests will be performed for the continuous variables, and chi-square tests for the categorical variables. To compare the effectiveness of the two treatment conditions, we will perform a multivariate analysis of variance for repeated measures (MANOVA) for the variables with subscales, and ANOVA for the single variables, taking the pretreatment, posttreatment and follow-up moments as within-subject factor and the treatment condition (FC vs TAU) as between-subject factor.

Moreover, between-group changes will be computed by calculating standardized effect sizes (Cohen’s d). Finally, we will perform zero-order correlations and linear regression analyses between the measures of the caregivers and the measures of the patients.

Because the trial is still going on, the state of the art in analytic methodology for RCT will be reviewed before analyzing the data, and so variations in the selection of the most appropriate analytic procedures may occur.

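### Two unranked primary outcomes with no success rule, one of them powered at the full 0.05: if either can carry the efficacy claim, the false-claim rate is about 8% to 10%, not 5%

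*Protocol article*

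**What the plan says.** - **Primary outcomes.** The Abstract (Methods) says "Primary outcome measures will be the BAS and FAD-GFS". The Primary outcomes section describes the same two scales without ranking them.
- **Sample size.** The calculation starts from "Considering an alpha of 0.05 and a statistical power of 0.80 on a 2-tailed" t test, with an assumed standardised difference of 0.60. The number needed "for burden is 90 participants (45 participants per experimental condition"). FAD-GFS has no calculation.
- **Times.** "Participants will be assessed at pre-, post-treatment, and 6-month follow-up". No time point is named as primary. The Study design section gives the follow-up measure the role of showing whether gains last.
- **Analysis.** The Data analyses section plans ANOVA for single variables and MANOVA for those with subscales, "taking the pretreatment, posttreatment and follow-up moments as within-subject factor" and treatment condition as the between-subject factor. It does not say whether the group effect or the group-by-time interaction decides.
- **Superiority hypothesis.** Hypothesis (b) in the Background reads "the FC program will significantly outperform the TAU intervention on measures of subjective burden, validation skills, family functioning, and quality of life". It names no time point and does not say how many of the four must succeed. The Abstract lists quality of life as secondary. Validation is covered by the VIRS, which appears under the patient measures.

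**The concern.** The 0.05 in the sample size calculation is the error rate of one test on one scale. Once two scales share primary status and each is tested at 0.05, it is the error rate of the trial's efficacy claim only if a rule makes it so. Examples are an order of testing, a split of alpha, or a requirement that both succeed. The article gives none of these.

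This matters in practice because the article ties consequences to its hypotheses being confirmed. The Ethics section makes the offer of FC to the TAU arm depend on it, and the Discussion expects rapid uptake in the centres. If burden improves and family functioning does not, or the reverse, nothing in the article says whether the hypotheses count as confirmed. Hypothesis (b) blurs this further by placing one secondary and one patient-reported construct beside the two primaries.

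**Working it through.** **Inputs from the article:** two primary outcomes; two-sided alpha 0.05; power 0.80; d = 0.60; 45 per arm before dropout; one repeated-measures model per outcome.

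**Assumed, because the article does not give them:** correlation between outcomes (0 to 0.8) and between times (0.5 to 0.8, or 0.6 in the ANOVA simulation).

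**1. The plan's own figure.** Two-sample t test, noncentral t, d = 0.60, two-sided 0.05: 44.6 per arm, so 45 per arm and 90 in total, with power 0.804. The stated number is reproduced. It covers one test on one outcome.

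**2. Two primary tests, either one sufficient.** With independent tests, the familywise error is 1 − 0.95² = 0.0975. With correlated tests it is 1 − P(|Z₁| < 1.96 and |Z₂| < 1.96) for a bivariate normal:

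| Correlation of the two tests | Familywise error | Multiple of 5% |
|---|---|---|
| 0 | 9.75% | 1.95 |
| 0.5 | 9.1% | 1.8 |
| 0.8 | 7.8% | 1.6 |

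**3. The same check on the planned model.** Two groups by three times were simulated under the null, with 45 per arm, within-subject correlation 0.6 and two outcomes. A significant group-by-time interaction on at least one outcome occurred in 9.8%, 9.7%, 8.9% and 8.6% of runs, at outcome correlations 0, 0.3, 0.5 and 0.7. This agrees with step 2.

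**4. What would push it higher.**
- Testing each outcome separately at post-treatment and at follow-up (four tests) gives 12.8% to 17.3%, for time correlations 0.5 to 0.8 and outcome correlations 0 to 0.7. The formula for four independent tests gives 1 − 0.95⁴ = 18.5%, but two scores from the same person are unlikely to be independent.
- Accepting either the group main effect or the interaction, on either outcome, gave 16% to 18% in the simulation of step 3.

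**5. If both primaries must succeed.** The error is at most 5%, so there is no inflation.

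**6. What the remedies cost in power (d = 0.60).**
- Alpha split 0.025/0.025: power at 45 per arm falls from 0.80 to 0.71. Restoring 0.80 needs 55 per arm, that is 110 completers instead of 90.
- Fixed sequence with BAS first: BAS keeps 0.05 and 0.80 at 45 per arm.

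**The case against.** **No either-or rule is written.** Hypothesis (b) joins its four constructs with an and. Read literally, all must succeed, and the error rate is then not inflated. This stands: the 8% to 10% is conditional on a rule the article neither states nor excludes. But (b) is worded as a scientific expectation, not a decision rule. It also mixes primary and other measures, so it does not settle how the two primaries combine.

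**Times are not separate tests.** A reader might infer that two outcomes at two post-baseline times give four routes to success and two to three times the nominal error. The article does not support this. The Data analyses section puts all three times in one within-subject factor per outcome, and the Study design section presents the 6-month measure as a check on maintenance. What remains is that the decisive effect in the model is not named, so the higher figures in step 4 are possible but are not the plan.

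**Multiplicity is often left to the SAP, and burden is evidently the lead outcome.** A missing adjustment procedure would not by itself be a finding in a condensed article. The point here rests on what the article does fix: two equal primaries, one alpha and one powered outcome. Sizing on burden suggests that BAS leads, but the outcome section gives FAD-GFS the same rank.

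**Conclusion.** The point holds in a limited form. The article gives BAS and FAD-GFS equal primary status, sizes the trial on burden at the full 0.05, analyses the scales separately and states no success rule. If either scale alone suffices, the chance of a false efficacy claim is about 8% to 10%, or 1.6 to 1.95 times the nominal level, for correlations between 0.8 and 0. That rests on two assumptions: the either-suffices rule and the correlation range. Figures of about 13% to 17% apply only with separate tests by time, under assumed correlations, and should not be quoted as a property of the plan. Apart from the error rate, a mixed result on the two primaries has no agreed interpretation in this article. It should be settled before the data are analysed.

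**What to change.** State in the protocol or SAP:

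1. The decisive contrast and the single time point for the primary test. The t test used for sizing and the repeated-measures model leave both open.
2. BAS tested first at two-sided 0.05.
3. FAD general functioning tested at two-sided 0.05 only if BAS is significant. Name that score explicitly, because the scale is described with seven subscales and could otherwise fall under the MANOVA.
4. The other time point, and the quality of life and validation measures in hypothesis (b), as secondary and without confirmatory claims. Reword (b) to match.

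This order holds the familywise error for the two primaries at 5%. If BAS has no true effect, a false claim requires a false positive on BAS. If BAS has a true effect, only the FAD test can be false, and it is done at 0.05. On the plan's own assumptions BAS keeps its power of 0.80, against 0.71 under an equal split, and no participants are added.

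The cost is a wording change and one real restriction: if BAS fails, a favourable FAD result cannot be presented as confirmatory.

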**Discussion:**

This is the first study on FC for relatives of people with borderline personality disorder (BPD) compared to an active condition (TAU), and this is the first time relatives’ and patients’ data will be analyzed. In addition, it is the first study to test the efficacy of the program in Spain. This intervention could contribute to improving the efficiency and effectiveness of current treatment programs for relatives of people with BPD, help to decrease burden, and improve the family connection.

**Trial registration:**

ClinicalTrials.gov ID: NCT04160871. Registered November 15th 2019.

## Background

Borderline personality disorder (BPD) is one of the most challenging and complex mental disorders. BPD is related to high suicide and self-harm rates. Persistent suicidal behavior is described in 69–80% of people with BPD [1]. A longitudinal study across 24 years comparing BPD and other personality disorders found that a total of 5.9% of BPD sufferers died by suicide and 14% by other causes, compared to 1.4 and 5.5% in a sample of people with other personality disorders [2]. BPD also involves high rates of hospital admissions and health service use. BPD is associated with a high economic burden due to the long-term use of health services [3–6], including interventions in emergency settings and the need for the services of several different professionals [6–8]. Furthermore, BPD is an important public mental health problem that produces great suffering for patients and their relatives [9]. For this reason, there is a need to provide specialized care.

The symptoms of BPD and their consequences lead to high levels of discomfort and burden for their relatives [10–14]. Additionally, there is evidence that maladaptive family communication patterns play a role in the etiology and maintenance of BPD [14, 15].

Family members of people with BPD are more likely to have psychological problems [16, 17], and they describe feelings of confusion, lack of awareness, and incompetence [14, 18, 19]. Studies with relatives of people with BPD showed that the levels of burden and depression can increase due to lack of clear knowledge about the diagnosis and the evolution of the disorder [19, 20]. Moreover, when family members participate in treatment, patient relapse decreases, recovery is easier, and wellbeing in the family improves [20, 21].

Currently, there are interventions for family members with empirical support. All these programs are offered in group format, but they differ in the type of orientation and contents. So far, two of these studies present only psychoeducational contents; one is based on mentalization [22], and the other combines cognitive analytical therapy with general psychiatric care [23]. Regarding the programs that offer skills training, almost all are DBT-based programs or DBT adaptations. These DBT skills training studies have different structures and numbers of sessions. They use either adaptations of DBT in 10–12 sessions where parents receive training in DBT mini-skills [17, 24–27] or group therapy where skills are taught for 6 months [28].

Family Connections (FC) is the most empirically supported program [25] for relatives of patients with BPD. The program can be carried out by clinicians or trained relatives. To date, five uncontrolled clinical trials have been performed with pre- and post-treatment and follow-up assessments [17, 24, 25, 29, 30]. In all the replications, the results of the FC program were consistent, showing significant decreases in burden, grief, anxiety, and depression, and significant increases in the participants’ subjective experience of mastery, empowerment, well-being variables, and family functioning. Furthermore, these variations were maintained or improved at 3- or 6-month follow up. The good results for family functioning could be due to the fact that FC validates patients’ skillful behaviors, decreases their psychological symptoms, improves interpersonal relationships between family members and patients, increases understanding of the problem, reduces perceived stigma, and enhances family empowerment [30].

FC is a program for relatives of people with BPD that was developed within the National Education Alliance for Borderline Personality Disorder [17, 25]. This program links three important needs for relatives: first, education about the disorder and family functioning; second, individual and family skills to manage negative reactions in the family and improve well-being in the relationship; and, finally, social support from other relatives participating in the same group who have had very similar experiences [17].

A pilot study by Hoffman et al. [25], with pre-, post-, and 6-month follow-up of one group, suggests that this program promotes significant reductions in grief and burden and a significant increase in mastery. A replication and extension study of FC by Hoffman et al. [17], with a pre-, post-, and 3-month follow-up of one group, shows improvements in well-being variables and depression. Another descriptive mixed study (qualitative and quantitative data) with two groups (family members with and without clinically relevant symptoms) showed that the subgroup with clinically relevant symptoms had a significant decrease in depression and anxiety symptoms at follow-up, and women showed a decrease in both anxiety and depression symptoms before and after the intervention [29]. Flynn et al. [24] found similar results in a non-randomized controlled study (pre-, post-, 3-, 12-, or 19-month follow-up) that compared FC with a psychoeducation group. Finally, in a non-randomized comparison study with pre-, post-, and 6-month follow-up assessments, participants who received FC reported fewer mental health difficulties, a lower perceived burden of caring, and higher overall family functioning [30].

Therefore, considerable progress has been made in this line of work, which had not previously been considered. However, it would be desirable to advance in this direction by comparing FC to active treatments in larger samples and, if possible, examine the impact of the treatment on both family members and patients. Another important issue is the dissemination of FC to other cultural contexts. This study will provide the first efficacy data on the comparison of FC with an active treatment condition in a randomized controlled trial. Another contribution of this study is the measurement of the evolution of the family climate in relation to the improvements of both relatives and patients. Finally, this is the first study on FC carried out in a Spanish-speaking population.

This study has several objectives. First, we aim to test the efficacy of FC for relatives of patients with BDP in an RCT with a sample of participants from specialized care in Spain, compared to Treatment as Usual (TAU), that is, an active treatment condition. Second, we will study the feasibility and acceptance of this intervention protocol in family members of patients with BPD. Third, we intend to study whether changes in family members’ disease burden and clinical symptoms are related to the improvements observed in patients with BPD. Fourth, we aim to study whether the changes that may occur in relatives with regard to disease burden and clinical symptoms are related to the family climate. Finally, we will study the perceptions and opinions of families and patients about both intervention protocols.

We hypothesize that: a) both interventions will result in significant reductions in distress and burden and improvements in overall family functioning at post-treatment, and these results will be maintained at the 6-month follow-up; b) the FC program will significantly outperform the TAU intervention on measures of subjective burden, validation skills, family functioning, and quality of life; c) both protocols will be well accepted, but FC will be rated significantly higher by the participants; d) the improvement that may occur in the family members with regard to disease burden and clinical symptoms will have a positive influence on the family climate; e) in an exploratory way, given the lack of specific data in the literature, we hypothesize that the changes observed in the relatives will be related to the clinical evolution of the patients. In this article, we present the study protocol.

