## Methods

### Study design

We will conduct a two-armed randomized controlled trial (RCT). Participants will be randomly assigned to one of two conditions: Family Connections (FC) or Treatment As Usual (TAU). Block randomization will be carried out among the three clinical centers, considering that if a patient has more than one family member who attends the group, they will be randomized together to be included in the same condition. Measures will be taken before starting the intervention, after the intervention, and at the 6-month follow-up to determine whether improvements after the intervention are maintained in the long term. The study flowchart appears in Fig. 1. We will follow the CONSORT statement (Consolidated Standards of Reporting Trials, http://www.consort-statement.org) [31, 32] and the SPIRIT guidelines (Standard Protocol Items: Recommendations for Interventional Trials) [33, 34].

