### Study population, recruitment, and eligibility criteria

The sample will consist of relatives of people with BPD. Recruitment will be carried out among relatives of patients treated at clinical centers specializing in the treatment of BPD in the Valencian region. Inclusion criteria will include the following: a) being 18 years old or more; b) having a family member diagnosed with BPD; c) ability to understand and read Spanish; and d) providing written informed consent. Participants will be recruited by clinicians working in these clinical centers in three Spanish cities (Castellón, Valencia, and Alicante), until the required sample is complete. Clinicians will offer patients’ families the opportunity to participate in the study and, after explaining it, obtain their informed consent. All the psychologists who participate in this research will have at least a master’s degree in Clinical Psychology and specialized FC training.

A psychologist will contact the participant to determine his/her inclusion in the study. At that time, the researcher will collect the baseline data and determine whether the inclusion criteria are met (see Table 1). Then the psychologist will contact a person outside the research group who will perform the individual randomization and inform the assessor of a code that corresponds to the type of treatment. This psychologist will be unaware of the characteristics of the study.

**Table 1 Tab1:** Study measures and evaluation times

Participant	Measure	Aim	Evaluation time
Caregiver	S-D Interview	Diagnosis	BL
	BAS	Severity of burden symptoms	BL, Post-T and FU
	FAD-GFS	Familiar Global Functioning	BL, Post-T and FU
	DASS-21	Depression, anxiety and stress symptoms	BL, Post-T and FU
	FES	Family empowerment	BL, Post-T and FU
	QLI-Sp	Quality of life	BL, Post-T and FU
	OTSM	Treatment opinion and acceptance	PM
Patient	FAD-GFS	Familiar Global Functioning	BL, Post-T and FU
	DASS-21	Depression, anxiety and stress symptoms	BL, Post-T and FU
	DERS	Difficulties in emotional regulation	BL, Post-T and FU
	LEAP	Emotional availability of parents	BL, Post-T and FU
	VIRS	Validating and invalidating responses	BL, Post-T and FU

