### Ethics

The study will follow the Declaration of Helsinki Guidelines and existing guidelines in Spain and the European Union for the protection of participants in clinical trials. The Ethics Committee of the University of Valencia (Valencia, Spain) has approved this study. The trial was registered at clinicalstrial.gov as NCT04160871, registered the 15th of November of 2019.

Sample recruitment will be carried out by qualified clinicians. Researchers will explain the study to the participants, and they will sign the consent form as volunteer participants with the possibility of dropping out at any time. If our hypotheses are confirmed, the FC condition will be offered to participants assigned to the TAU condition after the 6-month follow-up. Special difficulties are not expected, based on the literature. If a participant drops out of the trial due to unwanted events, s/he will have the opportunity to participate the next time the treatment groups for family members are offered.

To protect information, personal data (e.g. age, sex, address, mail, phone) will be collected by the researchers participating in this study, and data will be replaced by codes. Personal data will be strictly separated from other data, and it will only be available to researchers responsible for the study, always considering and protecting the right to privacy of the participants.

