#### Treatment as usual (TAU)

Treatment as usual is the program routinely offered to BPD patients’ relatives in the clinical centers participating in this trial. The intervention includes 12 therapeutic sessions in six modules. Each module has specific objectives and practical exercises.
*Introduction*. This module consists of an overview of the treatment and the aims of the group. Furthermore, it focuses on the definition of personality disorders, BPD and its clinical characteristics, the role of emotion regulation, and comorbid disorders.*Family Education*. The aim of this module is to explain the diagnostic criteria for BPD, associated problems (alcohol and substance use and eating disorders), the DBT model, and the main goals of the treatment.Validation Skills. The purpose of this module is to explain what validating and invalidating environments are, the consequences of an invalidating environment, and how to use validating skills.*Crisis Management Skills*. This module aims to prevent crises by explaining how to manage anger and learning how to act in the presence of self-injuring and suicidal behaviors. Moreover, acceptance skills are shown in this module.*Problem Management Skills*. This module helps the relative to know how to deal with problems and set clear limits, handle conflict in everyday situations, confront unacceptable behavior, and manage emotionally charged conversations.*Relapse Prevention*. It aims to strengthen the strategies learned throughout the program, schedule future practice, and teach the participants how to identify and cope with future high-risk situations.

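### Hypothesis (a) credits within-arm improvement to both programmes, but with two active arms and no untreated reference the design can support only the FC-versus-TAU contrast in hypothesis (b)

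*Protocol article*

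**What the plan says.** The Background lists two hypotheses that matter here.

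- Hypothesis (a) concerns change within each arm: "both interventions will result in significant reductions in distress and burden and improvements in overall family functioning at post-treatment". It adds that these results will persist at the 6-month follow-up.
- Hypothesis (b) concerns the difference between arms: "the FC program will significantly outperform the TAU intervention on measures of subjective burden, validation skills, family functioning, and quality of life".

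The Background describes the comparison as "compared to Treatment as Usual (TAU), that is, an active treatment condition". The section on TAU confirms this: "The intervention includes 12 therapeutic sessions in six modules", which matches the six modules and 12 sessions of FC. Study design names no third arm and no waiting period.

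The section on study population says: "Recruitment will be carried out among relatives of patients treated at clinical centers specializing in the treatment of BPD in the Valencian region".

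Data analyses plans a repeated-measures ANOVA or MANOVA, "taking the pretreatment, posttreatment and follow-up moments as within-subject factor and the treatment condition (FC vs TAU) as between-subject factor". It does not say which term of the model would answer hypothesis (a).

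The limitations in the Discussion are the number of centres and the length of follow-up. The absence of an untreated reference is not among them.

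**The concern.** Randomisation identifies the difference between FC and TAU. It does not identify what either programme achieves compared with no programme. Hypothesis (a) claims the latter for both, and its only evidence would be change from baseline within an arm.

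That change has rival explanations that this design cannot remove. Burden may ease with the natural course of the disorder. Relatives may join when things are at their worst. The patients are in specialist treatment at the same centres, and the protocol itself links relatives' burden to the patient's symptoms and expects relatives' changes to relate to the patients' clinical evolution.

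At stake is what the trial may conclude if FC and TAU turn out alike, which is possible for two programmes of the same length with overlapping content. As worded, hypothesis (a) would then permit the statement that both programmes work and that the gains last. The Background describes the existing FC evidence as uncontrolled pre-post studies. Hypothesis (a) repeats that type of inference inside a randomised trial.

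**Working it through.** **The plan's own figure.** The Sample size section uses d = 0.60, two-sided alpha 0.05, power 0.80 and equal arms. The two-sample t test with the noncentral t distribution gives n = 44.59, so 45 per arm and 90 in total. Power at 45 per arm is 0.804. The stated 90 reproduces. It is a between-arm calculation, so it belongs to hypothesis (b) and is untouched by this point.

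**What the design identifies.** Write the expected change in an arm as drift + programme effect, where drift covers everything that would have happened anyway, including the effect of the patient's own treatment.

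- FC change = drift + effect of FC
- TAU change = drift + effect of TAU
- FC change minus TAU change = effect of FC minus effect of TAU

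Drift cancels only in the third line. Two observed changes cannot determine three unknowns, so neither effect can be recovered on its own. An untreated arm would supply drift directly, and there is none.

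**How often drift alone would look like success.** The documents give neither a drift nor a pre-post correlation r, so both are assumed. Further assumptions are zero programme effect, equal SD at both times, one outcome, and a two-sided 5% paired t test in each arm with n = 45.

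- Standardised change: d_z = drift / sqrt(2(1 - r)), with drift in baseline SDs
- Noncentrality: d_z x sqrt(45)
- Both arms significant: (one-arm probability) squared, taking the arms as independent

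| Drift (SD) | r | d_z | One arm | Both arms |
|---|---|---|---|---|
| 0.20 | 0.5 | 0.200 | 0.259 | 0.067 |
| 0.20 | 0.6 | 0.224 | 0.311 | 0.097 |
| 0.20 | 0.7 | 0.258 | 0.395 | 0.156 |
| 0.30 | 0.5 | 0.300 | 0.503 | 0.253 |
| 0.30 | 0.6 | 0.335 | 0.595 | 0.354 |
| 0.30 | 0.7 | 0.387 | 0.719 | 0.518 |

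At a drift of 0.10 SD the one-arm probability is 0.101 to 0.135, and both arms reach significance in under 2% of trials. At 0.40 SD the figures are 0.747 to 0.923 for one arm and 0.558 to 0.852 for both.

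**Sensitivity to n.** If all 58 randomised per arm were analysed, a drift of 0.30 SD would give 0.613 to 0.826 for one arm and 0.375 to 0.683 for both.

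**The case against.** The strongest reply is that efficacy already rests mainly on the randomised contrast. The first objective compares FC with TAU, the sample size is a two-group calculation, and Data analyses presents its models as a comparison of the two conditions, with between-group effect sizes. No rule there says that a time effect proves both programmes work. On this view hypothesis (a) is one sentence of expectation, and careful interpretation can wait for the report. The description of the analysis is right and limits the point to hypothesis (a). It does not remove it: the sentence is causal, is judged by significance, and is nowhere called descriptive.

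Two stronger readings are tempting, and the documents do not support either.

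- A reader might infer that ordinary improvement would simply confirm (a), for example through the time effect pooled over arms. A pooled pre-post test on 90 would be significant 80-95% of the time at 0.30 SD drift. But (a) speaks of both interventions, so each arm must improve, and the relevant figure is 25-52% for one outcome. Because (a) also names distress, burden and family functioning, with maintenance at 6 months, requiring them all cannot raise that chance.
- A reader might infer that confirming (a) alone would lead to FC being offered to TAU participants or rolled out. The Ethics section says "If our hypotheses are confirmed, the FC condition will be offered to participants assigned to the TAU condition after the 6-month follow-up". The word is plural, as it is in the Discussion's remark on implementation. On the ordinary reading (b) must hold as well, so (a) alone triggers nothing. What stands is that neither section says which hypotheses are meant.

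The mechanisms should not be pressed too hard either. Eligibility sets no minimum burden or distress score, so regression to the mean from score-based selection does not arise. Help-seeking at a bad time remains possible but is undocumented. The Background says that BPD symptoms burden relatives, not that treating the patient lowers that burden. The BAS asks about the past 6 months, so the post-treatment score may overlap the period before treatment, which would damp short-term drift.

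**Conclusion.** The point holds in a limited form. The causal claim in hypothesis (a) cannot be supported by two active arms without an untreated reference, and no analysis of these data can change that. The reservation in Data analyses that methods may be revised therefore does not help.

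The size is illustrative. With no programme effect, one outcome would be significant in both arms 25-52% of the time at 0.30 SD drift and 7-16% at 0.20 SD. These figures rest on assumed drift, a pre-post correlation of 0.5 to 0.7, 45 analysed per arm, independent arms and equal drift in each. The identification argument does not depend on them.

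Hypothesis (b), the randomisation and the sample size are unaffected. Reporting within-arm change is legitimate; attributing it to the programmes is not.

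**What to change.** Four changes of wording:

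1. Restate hypothesis (a) as descriptive: change within each arm from baseline to post-treatment and to 6 months, reported with confidence intervals and not attributed to the programmes.
2. State that conclusions on efficacy rest on the randomised FC-TAU contrast in hypothesis (b).
3. Add the absence of an untreated reference to the limitations in the Discussion.
4. Reconcile the Ethics section and the implementation remark in the Discussion with the Background, so that it is clear which hypotheses must be confirmed. This asks only for consistency and proposes no rule for when FC is offered.

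Design, sample size and data collection stay as they are. The cost is in the claims: the trial can no longer conclude that TAU, or both programmes, are efficacious. If the arms do not differ, it can report how relatives changed, but not why.
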